**Timed appointment**

- special requirement (n=xx)

- other exclusion criteria (n=xx)

**Timed appointment**

- special requirement (n=xx)

- other exclusion criteria (n=xx)

**Open invitation**

- special requirement (n=xx)

- other exclusion criteria (n=xx)

Exclusion (n=xx)

- Lost to follow-up, e.g. women moved address (n=xx)

- Opt out screening

- Other reasons

Exclusion (n=xx)

- Lost to follow-up, e.g. women moved address (n=xx)

- Opt out screening

- Other reasons

Exclusion (n=xx)

- Lost to follow-up, e.g. women moved address (n=xx)

- Opt out screening

- Other reasons

Analysis

Exclusion (n=xx)

- special requirement (n=xx)

- other exclusion criteria (n=xx)

- wrong letters sent (n=xx)

- other admin errors (n=xx)

- other reasons (n=xx)

Exclusion (n=xx)

- special requirement (n=xx)

- other exclusion criteria (n=xx)

- wrong letters sent (n=xx)

- other admin errors (n=xx)

- other reasons (n=xx)

Exclusion (n=xx)

- special requirement (n=xx)

- other exclusion criteria (n=xx)

- wrong letters sent (n=xx)

- other admin errors (n=xx)

- other reasons (n=xx)

Exclusion (n=xx)

- special requirement (n=xx)

- other exclusion criteria (n=xx)

- wrong letters sent (n=xx)

- other admin errors (n=xx)

- other reasons (n=xx)

Follow-up

Exclusion (n=xx)

- Lost to follow-up, e.g. women moved address (n=xx)

- Opt out screening

- Other reasons

Open invitation

- special requirement (n=xx)
- other exclusion criteria (n=xx)

Timed appointment

- special requirement (n=xx)
- other exclusion criteria (n=xx)

Allocation (first letter)

Figure 2 Kaplan Meier graph of the primary endpoint by study arms

Figure 3 Kaplan Meier graph of the secondary endpoint by study arms

Figure 4 Other Kaplan Meier graph of primary/secondary endpoints by subgroup of interest

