## Inclusion / exclusion criteria

Women within the above services were eligible for this evaluation if they were due to be invited for their next breast screening appointment during the study period. Exclusions were made based on five criteria (as of section 5.2 of the evaluation protocol):

1. Opted out of the screening programme.
2. Require special appointments that require different types of clinics.
3. Self-referred for screening.
4. Women on an early recall protocol.
5. Women who are invited because they are high risk.

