## Preparing data for analysis

- The source dataset from each service has the same format and variables. To prepare a master file of all services the separate extracts must be joined together, with a new file to indicate which service each extract was from.

STATA command **Append** and **generate** a new variable *service* to indicate the source screening service.

- The joined dataset has each line representing one appointment, not per woman. To restructure the data so that each line represents a woman.

STATA command **reshape** from long to wide format using a unique identifier variable (*uniqueid)* and a variable tag each appointment (*[appointmenttag](#appointmenttag_create)*).

Record the total number of women in the final sample. ^1^

- Exclude all screenees who has special requirement based on [exclusion criteria](#inclusion_exclusion_criteria).

**Drop** if ‘Y’ in *specialrequirement.* Record the number of women in this group.^1^

- To assess for risk of bias later, ensure to flag all screenees with administrative errors, e.g. when a wrong type of invitation letter was sent (‘Y’ in *flag2oiinviteandnotaoicl* or in *flag3tabutanoiletterused)*, and keep a record of this number in each arm.^1^

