# Statistical Analysis

## General principles

**Analysis data**: Women who fall in the [exclusion criteria](#inclusion_exclusion_criteria) will be excluded from all analyses.

**Quantifying uncertainty:** Unless stated otherwise all p-values will be two-sided, and 95% confidence intervals used. There will be no adjustment for multiple testing unless specified.

**Missing data**: Primary analysis will include all women within the inclusion criteria and with complete data on primary endpoint. Details for dealing with missingness when deriving variable are in [section 3.2.2.](#derived_variables)

Overall, very low level of missingness is expected for any variable. In case of missingness on source data, all enquires will be first consulted with data team of the programme, to check whether this can be completed. If the problem cannot be solved, data imputation will be used for a variable, only if the missingness exceeds 80 screenees (5% of the total expected study participants).

**Reporting:** Statistical significance will be assessed at the two-sided 5% level unless otherwise stated. 95% confidence intervals will be provided as appropriate.

**Software**: The data management and analysis will be carried out using computer programme STATA version 17.0^6^.

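### Figure 1 lists wrong letters, moving and opting out as exclusions after allocation, which conflicts with the analysis text that keeps these women

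*SAP*

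**What the plan says.** Two parts of the SAP describe who is analysed.

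**The analysis text.** General principles states: "Primary analysis will include all women within the inclusion criteria and with complete data on primary endpoint". It also says that women who meet the exclusion criteria "will be excluded from all analyses". Inclusion / exclusion criteria gives five of these. The first is "Opted out of the screening programme"; no date is attached to it here, and the list refers to section 5.2 of the protocol. Moving house and receiving the wrong letter are not among the five.

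Preparing data for analysis contains one drop instruction, "Exclude all screenees who has special requirement based on" the exclusion criteria. For wrong letters it says only to "ensure to flag all screenees with administrative errors" and to count them by arm. Other analysis then allows an exploratory look at bias from such errors. Data linkage and variable derivation codes a woman with no attended appointment as 0 on the primary endpoint, and Primary endpoint methods uses the number of women invited as the offset.

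**The flow diagram.** The Figure 1 template in the appendix has four exclusion boxes that list "Lost to follow-up, e.g. women moved address (n=xx", "Opt out screening" and other reasons. Four more list "wrong letters sent (n=xx", other administrative errors and other reasons, besides special requirement and other exclusion criteria. Its stage labels include follow-up and analysis as well as the allocation of the first and second letters.

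**The concern.** The two descriptions lead to different primary datasets. Under the analysis text, a woman allocated to an arm and invited stays in it whatever happens next. Under the diagram, she can leave because of something that happened after allocation.

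Those events are not neutral:

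- **Opting out after the letter** may be a response to the invitation strategy, and it is a non-attendance. Removing the woman takes a failure of the strategy out of the denominator.
- **Moving without attending** has the same arithmetic effect.
- **Wrong letters** depend on the letter type that was due: the source-data table defines one flag for an open letter used in error and another for a timed letter used in error. Removing these women is a per-protocol-type exclusion related to arm. It can remove attenders as well as non-attenders.

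At stake is the like-for-like comparison that allocation by identifier digits is meant to give. If the removed shares differ between timed and open strategies, the arm contrast is distorted.

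**Working it through.** **Step 1: compare the rules group by group.**

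| Group | Analysis text | Figure 1 template |
| --- | --- | --- |
| Wrong letter | Flagged, counted by arm, possible exploratory analysis; not one of the five criteria | Under an exclusion heading |
| Moved address | Not one of the five criteria; coded 0 if no attendance is recorded | Under an exclusion heading |
| Opted out | Criterion 1, no cut-off given in the SAP, applied to all analyses; otherwise coded 0 | Under an exclusion heading, beside loss to follow-up |

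For wrong letters the conflict is direct. For movers the diagram adds an exclusion that the text does not authorise. For opt-outs the fault is the undated criterion combined with its second appearance beside loss to follow-up.

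**Step 2: check the planning figures used below.** Sample Size Justification gives 65% v 73%, 80% power, two-sided 5%, 524 per group, and 4,000 per arm overall. With pooled variance and mean rate 0.69:

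n = [1.960 × √(2 × 0.69 × 0.31) + 0.842 × √(0.65 × 0.35 + 0.73 × 0.27)]² / 0.08² = 523.5, rounded up to 524. The plan's figure is reproduced.

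**Step 3: illustrate the effect of removal.** The SAP gives no shares, so these are assumptions. Let d be the share of all invited women in an arm who are non-attenders and are removed. The observed rate is then the true rate / (1 − d).

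| d timed | d open | Timed | Open | Difference | Ratio |
| --- | --- | --- | --- | --- | --- |
| 0 | 0 | 73.0% | 65.0% | 8.0 points | 1.123 |
| 1% | 1% | 73.7% | 65.7% | 8.1 points | 1.123 |
| 5% | 5% | 76.8% | 68.4% | 8.4 points | 1.123 |
| 1% | 3% | 73.7% | 67.0% | 6.7 points | 1.100 |
| 3% | 1% | 75.3% | 65.7% | 9.6 points | 1.146 |

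For example, 0.73/0.99 = 0.7374, 0.65/0.97 = 0.6701, and the difference is 0.0673.

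**Step 4: the same under no true effect.** With 65% in both arms, 4,000 allocated to each, and d of 1% and 3%, the spurious difference is 0.65/0.99 − 0.65/0.97 = −0.0135. The analysed numbers are 3,960 and 3,880, and the pooled rate is 5,200/7,840 = 0.663. The standard error is √(0.663 × 0.337 × (1/3,960 + 1/3,880)) = 0.0107, so the test statistic is shifted by −1.27. The two-sided false-positive rate is then about 25% instead of 5%.

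**Step 5: how far this depends on the meaning of the share.** If 1% and 3% are shares of the non-attenders rather than of all invited women, the null-case bias is 0.65/(1 − 0.35 × 0.01) − 0.65/(1 − 0.35 × 0.03) = 0.6523 − 0.6569, about −0.46 points. That is roughly a third of the figure in Step 4.

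Steps 3 to 5 concern removed non-attenders only. They do not apply to wrong-letter women, whose attendance is mixed.

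**The case against.** The strongest reply is that the operative text would keep most of these women. The only programmed drop is for special requirement, non-attendance is coded 0, the offset is the number invited, and no analysis variable uses the reason for episode closure. On that view, the exclusions rest on an unfilled figure template. This stands. A reader might infer that the plan as written deletes non-attenders from the primary denominator, but the documents do not support that. They support a contradiction that would have this result if the diagram were followed.

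Other parts of the reply also stand:

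- **Opt-out timing.** A reader might infer that opt-outs are excluded without any time limit. The criteria read naturally as status when invitations are issued, and a cut-off may be in protocol section 5.2, which is not at hand. Only the SAP's silence and the diagram's repeat listing can be criticised.
- **Inflation in every arm.** This is not shown. Wrong-letter women include attenders, and the SAP expects them to be very few.
- **Movers.** The primary analysis requires complete endpoint data, so leaving out a woman whose endpoint is truly unknown need not contradict it. However, the coding rule gives 0 wherever no attendance is recorded.
- **Layout.** The drawing was flattened in extraction. The exclusion headings and stage labels are in the text, but which box belongs to which stage is partly reconstructed.
- **Existing provision.** Wrong letters are already counted by arm and may be explored. That analysis is optional and its form is not fixed.

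None of this removes the direct conflict over wrong letters or the unauthorised exclusion of movers.

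**Conclusion.** The point holds as a contradiction that should be reconciled. Figure 1 shows as exclusions women whom the analysis text keeps (wrong letters, movers), and it lists opt-outs beside loss to follow-up while the SAP's own criterion has no cut-off.

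The size and direction of any bias are unknown because the documents give no shares. Under the assumed 1% and 3% of all invited women, the design contrast of 8.0 points would be reported as 6.7 or 9.6, depending on which arm loses more. Equal shares leave the ratio, which is the plan's primary measure, unchanged. A reader might take one of these figures as the expected bias; neither the split nor its direction has any support in the SAP. The sample size is unaffected.

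**What to change.** 1. In General principles, define the primary set as all women eligible on status recorded before the first letter, analysed in the arm to which they were allocated. Apply all five exclusion criteria at that point.
2. State that later opt-outs and movers with no recorded attendance are coded 0.
3. State that wrong-letter women stay in their allocated arm.
4. In Figure 1, show later opt-outs, movers, wrong letters and other administrative errors as counts by arm, not as removals.
5. Replace the optional exploratory analysis with one specified sensitivity analysis of the primary endpoint that leaves out women with *flagadminerror* equal to 1.

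The cost is a few lines of SAP text and an edit to the diagram. The administrative-error flag and letter print date are already listed. The data dictionary shows a reason for episode closure but no opt-out date, so the data team may need to confirm which opt-outs came before the first letter. The downside is that reported attendance may be slightly lower.
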